#### Establishing equivalency among study sites

For each nutrient and time period, pairwise comparisons using the 2, 1-sided test (TOST) method will be used to compare the means of the 4 sites for equivalence (20). If differences >0.3 SD are detected, a follow-up test will be conducted to compare each mean to the combined means of the other 3 sites, to determine which sites can be pooled. A sample size of 200 per site in each time period is sufficient to detect differences of 0.25 SD with 80% power or differences of 0.30 SD with 90% power. Therefore, the planned sample size of 250 per site and time period will provide adequate power to determine whether 1 site is different from the others (**Table 5**).

**TABLE 5 tbl5:** Required sample sizes for testing equivalence

Differences (site means)	Sample size/site 80% power	Sample size/site 80% power
0.20 SD	310	429
0.25 SD	199	275
0.30 SD	139	191

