## Methods

### Study design and settings

The MILQ Study is a multi-center, collaborative project with data and sample collection in 4 countries, Bangladesh, Brazil, Denmark, and The Gambia. Samples and data (e.g. anthropometry, questionnaires) are collected from 250 mother-infant dyads per country site (*n *= 1000 mothers and 1000 infants) in a systematic, identical way across sites for colostrum (1–2 d postpartum), and at 3 subsequent time points: 1.0–3.49 mo (visit 2), 3.5–5.99 mo (visit 3), and 6.0–8.5 mo (visit 4) postpartum (*n* = 1000 dyads). Within each time window the collection of samples is randomized so that some samples and data are available for almost every day between 1 and 8.5 mo postpartum, enabling smoothing of reference curves. Visits 2 through 4 are divided into 3- or 4-wk time periods. If a participant's first visit is randomly assigned to the first week of a time period, then their second and third visits are also scheduled in the first week of the time block. To evaluate the effect of intraperson variability on outcome variables, a subset of 50 women in Bangladesh, Brazil, and The Gambia are providing a second milk sample on visits 2 and 3. Details about each study location and analytical site are provided in **Tables 1** and **2**.

**TABLE 1 tbl1:** Study settings, and participant information in the Mothers, Infants, and Lactation Quality (MILQ) Study

	Bangladesh	Brazil	Denmark	The Gambia
Location	Mirpur (periurban area of Dhaka)	Madureira and São Cristóvão (Rio de Janeiro)	Copenhagen Rigshospitalet	Bakau and Fajara urban Gambia near Banjul
Average income, USD/mo	245	456	3120	247
Literacy, %	69	93	100	>65
Maternity leave, mo	6^1^	4–6	9–12	6
EBF, %				
2 mo	_	50	71	70
4 mo	_	_	60	_
6 mo	55	_	_	47
Infant stunting at 6 mo, %	18.6	4.8	<1	9
Usual diet	Rice	Rice and beans	Typical Western diet	Rice and maize
	Fruit and vegetables	Fruit and vegetables	Animal source foods, dairy	Fruit and vegetables
	Some animal source foods	Animal source foods, dairy		Groundnuts
		Pasta, high-processed foods		Some animal source foods
MMN supplementation	No, unless prescribed		Some, but not in this study	No
*Government mandates or recommendations*				
Perinatal	_	_	Iron and folic acid	_
Pregnancy	_	Iron and folic acid	Vitamin D	Iron and folic acid
	_	_	Calcium (low cow milk intake)	_
Fortification programs	No	Iron and folic acid (flour)	Iodine (salt)	No

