## Discussion

Although the importance of human milk in maternal and infant nutrition has long been recognized, the MN intake recommendations for breastfeeding infants and lactating women are still based on old, uncertain, or even incorrect data (4) and are established mainly as Adequate Intakes for infants due to the lack of experimentally determined estimates of milk composition and nutrient requirements (23). Further, the dynamic changes in concentrations of many milk nutrients across lactation are not reflected in the current recommendations, which can lead to erroneous status evaluations (24, 25). Therefore, given the importance of adequate nutrient intake during the first 1000 d of life (26), which includes the WHO-recommended 6-mo period of EBF (1), this systematic, longitudinal assessment of the nutrient composition of human milk, in particular for MNs, using validated methodologies, is indispensable for correctly evaluating nutrient intake adequacy of breastfeeding infants.

We have developed and validated multiple novel methods for collecting and analyzing human milk (24, 27–30), which will be used or further optimized for the nutrient assessment in this study. The identical collection protocols and methods for analyzing human milk and blood samples minimize method bias and enable direct comparison between field sites. The inclusion and exclusion criteria, and collection of information on diets, anthropometry, and infant developmental milestones provide supportive information that participants are healthy and nutrient sufficient.

The 4 field sites are different in demographics, socioeconomic status, diets, and cultural practices which may preclude combining data across sites to establish the RVs, but the required number of participants per site allows for the creation of study-site-specific RVs if necessary.

The longitudinal data obtained by the staggered sample collection protocol will allow for the development of new dynamic RVs, providing percentile ranges for every stage of lactation covered in this study. These carefully developed RVs, in conjunction with the milk volume data, will be available for re-evaluating intake recommendations for infants, young children, and lactating women, and as benchmarks against which to evaluate human milk quality, and the effects of future nutrient intervention trials on milk composition.

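### The site-equivalence TOST is worded on window means with no term for day postpartum, and the SD behind the 0.3 SD margin is not defined

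*Protocol article*

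**What the plan says.** Under *Establishing equivalency among study sites*, the protocol article plans, for each nutrient and time period, that "pairwise comparisons using the 2, 1-sided test (TOST) method will be used to compare the means of the 4 sites". The trigger for further testing is on an SD scale: "If differences >0.3 SD are detected, a follow-up test will be conducted". Neither sentence mentions age or day postpartum, and neither says whether the SD is that of all values in the window or a residual SD from a model.

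The sample-size support is in the same section: "A sample size of 200 per site in each time period is sufficient to detect differences of 0.25 SD with 80% power", and "the planned sample size of 250 per site and time period will provide adequate power". Table 5 gives the required numbers per site, for example "0.25 SD 199 275".

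*Study design and settings* defines the periods as "1.0–3.49 mo (visit 2), 3.5–5.99 mo (visit 3), and 6.0–8.5 mo (visit 4) postpartum" and adds: "Within each time window the collection of samples is randomized so that some samples and data are available for almost every day". *Specimen collection* says the collection form records day and time. The Discussion promises dynamic reference values, "providing percentile ranges for every stage of lactation covered in this study".

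Two other places bear on the reading. *Estimating centiles* foresees regression models for the distribution parameters, lets the mean and SD be either sample or model-based quantities, and leaves the model open until data exist. *Data analysis plan* refers back to the described method for comparing parameters among sites. It also allows pooling where site differences do not matter for the key percentiles.

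**The concern.** The product of the study is a set of centile curves over age, and sampling was spread over each window to support them. The test that decides whether sites are combined is worded as a comparison of window means. If those means are raw, any rise or fall of a nutrient across the 2.5 months is counted as random variation. It then enters the standard error. If the margin is in units of the same SD, it enters the margin as well.

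What is at stake is either some avoidable loss of power in the pooling decision or a margin somewhat wider than 0.3 SD on the age-specific scale on which the curves are read. Which of the two applies depends on what 0.3 SD means, and the article does not say.

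**Working it through.** **1. The plan's own figures.** The significance level is not stated. One-sided 0.05 with SD = 1 fits Table 5:

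n per site = 2 × ((z₀.₉₅ + z_power) / d)²

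- d = 0.25, 80% power: 2 × ((1.645 + 0.842)/0.25)² gives 198 (stated 199).
- d = 0.25, 90% power: 2 × ((1.645 + 1.282)/0.25)² gives 275 (stated 275).
- The other rows give 310 and 429 for 0.20 SD, and 138 and 191 for 0.30 SD (stated 310, 429, 139, 191).

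The second column matches 90% power, as the text implies, although both columns are headed 80%. The calculation is a plain two-sample one with no covariate.

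**2. TOST power as planned.** For one pair with n = 250 per site, no true difference and margin m:

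power = 2 × Φ(m/se − 1.645) − 1, with se = SD × √(2/n)

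With m = 0.3 SD, se = √(2/250) = 0.0894 SD and m/se = 3.354. Power = 2 × Φ(1.709) − 1 = 91.3%.

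**3. Effect of age.** Let R² be the share of within-window variance explained by day postpartum, so that residual SD = raw SD × √(1 − R²). The documents give no age trend, so R² is an assumption, taken here from 0.02 to 0.20. For scale, a linear change of k residual SD across a window with uniform timing gives R² = (k²/12)/(1 + k²/12): 0.02 for k = 0.5, 0.077 for k = 1 and 0.158 for k = 1.5.

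*Reading A: the margin stays at 0.3 raw SD.* Adjustment shrinks se to 0.0894 × √(1 − R²) raw SD and leaves the margin alone.

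*Reading B: the margin is meant in residual SD.* A margin of 0.3 raw SD equals 0.3/√(1 − R²) residual SD.

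| R² | A: se (raw SD) | A: one-pair power, adjusted | B: 0.3 raw SD in residual SD | B: excess width |
|---|---|---|---|---|
| 0 | 0.0894 | 91.3% | 0.300 | 0% |
| 0.02 | 0.0885 | 91.9% | 0.303 | 1% |
| 0.05 | 0.0872 | 92.8% | 0.308 | 3% |
| 0.10 | 0.0849 | 94.1% | 0.316 | 5% |
| 0.20 | 0.0800 | 96.5% | 0.335 | 12% |

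Under reading B, margin and standard error shrink together, so the adjusted test at 0.3 residual SD also has 91.3% power at zero difference, whatever R² is. What changes is strictness. With a true difference of 0.1 residual SD and R² = 0.10, the raw test passes 73.9% of the time and the adjusted test 72.1%.

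**4. Chance imbalance in age.** Assume uniform timing over about 76 days. The SD of sampling day is then 76/√12 ≈ 22 days, and the SE of the difference in mean age between two sites of 250 is 22 × √(2/250) ≈ 2 days.

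**The case against.** The strongest reply is that the article never calls the comparison unadjusted. *Estimating centiles* allows model-based means and SDs, *Data analysis plan* compares parameters among sites, and the choice of covariates is ordinary content for an analysis plan that is not shown. This stands in part. A reader might infer that the protocol prescribes raw means, but that is only the natural reading of the TOST paragraph. The regression passage concerns centile estimation by time period, however, and nothing links it to the TOST. The undefined SD is a gap in the stated rule itself.

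Three stronger inferences are not supported.

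- **Power loss and a wider margin together.** Against any one adjusted test these are alternatives. If the absolute margin is fixed, power is lost and nothing is widened. If the margin follows the SD, it widens and power at zero difference does not change.
- **Large gains when all six pairs must pass.** Simulated power for all six pairs is about 68% unadjusted, 77% at R² = 0.10 and 85% at R² = 0.20. No rule in the article requires all six to pass: there is a follow-up test of each site against the other three, pooling of two or three sites is allowed, and so is pooling where key percentiles are not materially affected.
- **Bias from visit timing.** Timing is randomised within windows. A one-week gap in mean sampling age would be about 7/1.96 ≈ 3.6 standard errors. It would need systematic departures from schedule at a site, which the documents do not suggest.

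**Conclusion.** The point holds as a modest matter of efficiency and margin definition. As worded, the pooling test compares means over windows of about 2.5 months without using the recorded collection day, and its margin can be read on two scales.

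If raw means are used and the margin is 0.3 raw SD, adjustment would add roughly 0.6 to 5 percentage points to one-pair power of 91.3%. If the margin is meant on the age-specific scale, using the raw SD makes it 1–12% too wide at unchanged power. Both ranges rest on an assumed R² of 0.02–0.20, one-sided 0.05, 250 per site and, for power, no true difference. For nutrients with flat trends (R² of 0.05 or less), the gain is under 2 points. No bias is expected in either case.

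**What to change.** For each nutrient and period, fit the transformed concentration on site and a smooth function of exact days postpartum. Run the TOST on the resulting site contrasts, with the residual SD in the standard error. State in advance which SD defines 0.3 SD:

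- the raw window SD, which keeps the present absolute margin and gains the power shown above; or
- the residual SD, which matches the scale of the age-specific curves, makes the test slightly stricter and leaves power at zero difference at 91.3%.

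The cost is one covariate in a regression that the article already foresees, plus a sentence defining the margin. Collection day is already recorded, and no change to sample size or fieldwork is needed.

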### Statistical analysis

#### Sample size calculations

Since the primary outcome is estimated key centiles of the distributions of nutrient concentrations in human milk, and centiles are invariant to monotonic transformation, sample sizes for constructing RVs are based on: *1*) estimating the 50th and 5th percentiles of each breast milk nutrient across time periods within each site and *2*) being able to establish equivalency among study sites before pooling data.

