**FIGURE 3 fig3:**
[figure not shown]
Hypothetical graphical illustration of reference values that may result for a micronutrient.

For each nutrient and time period, the distribution of the human milk variable will be examined and extreme outliers will be investigated and, if needed, removed. Box–Cox and other transformations will be used to normalize each variable, preferably using the same transformation across study sites, and the Shapiro–Wilk statistic to assess normality; skewness, kurtosis. The general shape of the distribution will also be examined. Parameters will be compared among study sites as described above, and information from the sites will be combined if the sites are deemed to be equivalent, or if differences have no material effect on key percentiles; otherwise, different sets of RV centiles may be constructed per site, or with only 2 or 3 pooled sites.

Parameters from the identified distribution will be estimated from the data, and centiles of interest (5th, 25th, 50th, 75th, 95th) will be estimated for each nutrient based on the theoretical percentiles of the underlying distribution, as described above. Smoothing techniques such as cubic splines will be employed, assuming the centiles follow smooth and continuous functions. Tables and curves of estimated centiles will be created for each nutrient and time period. SAS for Windows Release 9.4 (SAS Institute) will be used for all analyses.

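### Sites can be pooled on equivalent means alone, although the outer reference centiles also depend on each site's SD

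*Protocol article*

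**What the plan says.** The article's sample size section states that "the primary outcome is estimated key centiles of the distributions of nutrient concentrations in human milk". The introduction sets the reference range at the 2.5th to 97.5th percentiles, from the four sites combined. The section on estimating centiles computes each one as the mean plus a normal quantile times the SD.

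Pooling is governed by two passages:

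- **Establishing equivalency among study sites.** By nutrient and period, pairwise TOST "will be used to compare the means of the 4 sites for equivalence". When a difference above 0.3 SD is found, the follow-up, again on means, must "compare each mean to the combined means of the other 3 sites, to determine which sites can be pooled". Table 5 is likewise in terms of differences between site means.
- **Data analysis plan.** Parameters are to be compared in the manner already described. The pooling rule then reads: "information from the sites will be combined if the sites are deemed to be equivalent, or if differences have no material effect on key percentiles". Failing both conditions, centiles may be built per site, or from two or three pooled sites.

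No comparison of SDs is specified anywhere. Outer centiles enter only through the second limb of the pooling sentence.

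**The concern.** A centile other than the median depends on two parameters, and the equivalence test looks at one. At the 5th centile a difference of one unit in the SD moves the limit by 1.645 units; at the 2.5th, by 1.96. Because the two conditions are joined by 'or', the percentile criterion can rescue sites that fail on means but cannot stop sites that pass on means.

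The lower centile matters most, because the discussion section offers these values as benchmarks for milk quality and for revising intake recommendations. If spread differs between pooled sites, the pooled lower limit is too low for the narrow sites and too high for the wide ones. Across all sites together the share below it can still look close to nominal, so the misfit shows only when results are split by site.

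**Working it through.** **Inputs.** From the article: 250 women per site and period, a 0.3 SD margin, four sites, and centile = mean + Z × SD. Assumed: one-sided alpha 0.05 for each test (not stated), equal site means on the transformed scale, normality, and SD ratios of 1.1 to 1.3 (none is given).

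**1. The plan's own figure.** Table 5 follows from n = 2(z₀.₉₅ + z_power)²/d².
- 80% power: 2 × (1.645 + 0.842)² = 12.37, giving 310, 198 and 138 for d = 0.20, 0.25 and 0.30. The table has 310, 199 and 139.
- 90% power: 2 × (1.645 + 1.282)² = 17.13, giving 429, 275 and 191, as in the second column. Both columns are headed 80%, but the text shows that the second is 90%.

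This supports the assumed alpha. The formula contains only a difference in means and a common SD.

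**2. Misfit after pooling.** Three sites have SD 1 and one has SD 1.3.
- Pooled SD = √((3 + 1.69)/4) = 1.083.
- Pooled 5th centile = −1.645 × 1.083 = −1.781. Share below: Φ(−1.781) = 3.7% at the narrow sites and Φ(−1.781/1.3) = 8.5% at the wide site.
- Pooled 2.5th centile = −1.96 × 1.083 = −2.122. Share below: 1.7% and 5.1%.

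**3. How the size varies with the ratio r.** The gap between the wide and narrow sites' own 5th centiles, in pooled SDs, is 1.645(r − 1)/s_pooled.

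| r | Pooled SD | Gap at 5th centile | Below pooled 5th, narrow / wide |
|---|---|---|---|
| 1.1 | 1.026 | 0.16 | 4.6% / 6.2% |
| 1.2 | 1.054 | 0.31 | 4.2% / 7.4% |
| 1.3 | 1.083 | 0.46 | 3.7% / 8.5% |

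A ratio near 1.2 therefore separates the 5th centiles by as much as the plan's own 0.3 SD limit for means.

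**4. Does the means test react to spread?** With equal means, TOST passes with probability 2Φ(m/se − 1.645) − 1. For a narrow-wide pair at r = 1.3, se = √((1 + 1.69)/250) = 0.1037. The article does not say which SD defines the margin m:
- pair-pooled SD: m = 0.3 × 1.160 = 0.348, pass 91%
- four-site SD: m = 0.3 × 1.083 = 0.325, pass 86%
- smaller SD: m = 0.300, pass 79%

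With equal SDs the figure is also 91%. In simulation, all six pairs pass in about 68% of runs both at r = 1 and at r = 1.3 when the margin uses the pair-pooled SD. With the smaller-SD margin the rate falls from about 63% to about 49%, so that choice gives some sensitivity to spread, but by accident and weakly.

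**The case against.** **'Parameters' may include the SD.** The data analysis plan uses the plural, and elsewhere the word covers mean and SD. But the sentence refers back to the comparison already described, and that is a test of means with a follow-up test of means.

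**The distributions are examined anyway.** This stands in part. Skewness, kurtosis, shape and normality are inspected, and unpooled centiles are allowed, so a marked difference in spread could be noticed. It would be too strong to infer that it must go unseen. Still, nothing requires an SD comparison by site, a common Box-Cox transformation does not equalise spread, and in simulated pooled data with one site at SD 1.3 Shapiro-Wilk rejected in only about 18% of runs.

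**The detail belongs in an SAP that is not shown.** That holds for a numerical tolerance. It does not hold for the rule, which the article states itself.

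**The plan already tolerates similar misfit.** With equal SDs and one site 0.3 SD lower, 4.1% and 7.6% fall below the pooled 5th centile. True, but a true difference at the margin passes a TOST only 5% of the time, whereas equal means with unequal SDs pass 79% to 91% of the time.

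**The size is assumed.** This stands. A reader might infer that the reference values will be wrong, or that 91% is the chance that all four sites are pooled. The documents support neither: they give no SD ratio, and 91% concerns one pair under one margin. Pooling all four on means needs six passes.

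**Conclusion.** The point holds as a defect in a stated rule. Passing TOST on means is sufficient for pooling, while the primary product depends on the SD as well. The logic does not rest on any assumed figure.

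The consequence does. It needs a real difference in spread on the transformed scale: minor at a ratio of 1.1, equal to the plan's own tolerance at about 1.2, and 3.7% against 8.5% below a nominal 5% limit at 1.3 with one wide site. The discussion section says that the sites differ in diet and socioeconomic status, which makes unequal spread plausible but does not establish it. Because the size is conditional and site-specific centiles are already provided for, this is a should-fix. The documents do not support calling it an established error in the reference values.

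**What to change.** 1. Reword the pooling sentence so that the key-percentile criterion must be met before any pooling, including when the means pass TOST.
2. For each nutrient and period, report the ratio of site SDs on the common transformed scale with a 90% CI. At 250 per site an F test detects a ratio of 1.3 with 98% power.
3. Compare each site's own outer centiles with the pooled ones against a pre-set limit on the difference, for example the existing 0.3 SD margin. Name the SD that defines it.
4. Where means agree but SDs do not, fit a site-specific SD or use the site-specific or partly pooled centiles that the plan already allows.

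Two cautions on the limit:
- A band such as 2.3% to 7.7% below the pooled 5th centile (the sampling range at n=250) is not suitable. It is a non-rejection range: it would accept two sites at SD 1 and two at 1.3 (2.8% and 7.1%), and would catch the 8.5% site only about 64% of the time.
- A site-to-pooled limit of 0.3 SD catches the wide site in the one-wide-site case at 1.3, since 1.645 × (1.3 − 1.083)/1.083 = 0.33. It does not catch the two-against-two case, where the pooled SD is 1.160 and the differences are 1.645 × 0.140/1.160 = 0.20 and 1.645 × 0.160/1.160 = 0.23. The SD ratio in step 2 therefore needs its own pre-set limit.

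The cost is a sentence or two in the plan and a few lines of code, with no new data. The downside is that some nutrients that would have been pooled on means will not be, and their centiles will rest on fewer women.

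### The one-versus-other-three follow-up cannot identify a two-versus-two split of sites, and it rejects matching sites when one site is far off

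*Protocol article*

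**What the plan says.** The section on establishing equivalency among study sites sets two steps for each nutrient and time period. First, "pairwise comparisons using the 2, 1-sided test (TOST) method will be used to compare the means of the 4 sites for equivalence". Second, "If differences >0.3 SD are detected, a follow-up test will be conducted", whose task is to "compare each mean to the combined means of the other 3 sites, to determine which sites can be pooled". The power statement says that "the planned sample size of 250 per site and time period" "will provide adequate power to determine whether 1 site is different from the others".

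The Data analysis plan (text after Figure 3) refers back to this comparison. It pools sites that are equivalent, or whose differences leave the important centiles essentially unchanged. Otherwise, "different sets of RV centiles may be constructed per site, or with only 2 or 3 pooled sites". It gives no other rule for choosing the two or three sites. The Discussion accepts that differences between the sites "may preclude combining data across sites to establish the RVs".

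**The concern.** The follow-up decides whose data form each primary reference set. It measures each site against an average of the other three, and that average includes any deviant site. Two high and two low sites therefore all appear equally far from the rest, and one extreme site pulls the comparator away from the three sites that agree. The power statement considers only a single deviating site, whereas the Data analysis plan foresees pools of two or three.

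The risk is that sound pooling is refused, with less precise and more fragmented reference values. On one reading of the follow-up, sites further apart than the plan's own limit could instead be pooled. Table 1 shows monthly incomes of USD 245, 456, 3120 and 247 and differing diets, so more than one pattern of site differences is possible across many nutrients.

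**Working it through.** **Inputs.** From the equivalency section: 250 per site and period, and a limit of 0.3 SD. Assumptions: SD 1 at every site; the 0.3 SD limit also serves as the TOST margin; one-sided alpha 0.05, which is not stated but is inferred from Table 5; site differences D and d, which the article does not give in SD units and which are varied below.

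**The plan's own figures.** n per site = 2(z₀.₉₅ + z_power)²/δ².
- 80% power: 2(1.645 + 0.842)²/δ² gives 310, 198 and 138 for δ = 0.20, 0.25 and 0.30. Table 5 prints 310, 199 and 139.
- 90% power: 2(1.645 + 1.282)²/δ² gives 429, 275 and 191, as in the second column of Table 5 (whose heading also says 80%).

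Table 5 is thus reproduced to within one. A two-sided 0.05 test would need 393, 252 and 175 at 80% power and does not match.

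**The contrast.** c = site mean − mean of the other three.
- Two against two, means (0, 0, D, D): a low site gives 0 − (0 + D + D)/3 = −2D/3, and a high site gives D − (0 + 0 + D)/3 = +2D/3. All four have the same size. It reaches 0.3 at D = 0.45. Between 0.30 and 0.45 no true contrast exceeds the limit although the groups do; above 0.45 all four exceed it although each pair is identical.
- One outlier, means (d, 0, 0, 0): the outlier gives d, and each other site gives −d/3. The latter reaches 0.3 at d = 0.9.

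**Pass and flag rules.** The article does not state the form of the follow-up, so two main readings are shown.
- SE(c) = √(1/250 + 1/750) = 0.073. A TOST passes if |c| < 0.3 − 1.645 × 0.073 = 0.180.
- On point estimates a site is flagged if |c| > 0.3.

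Per-site checks by formula:
- D = 0.40, TOST pass: Φ((0.180 − 0.267)/0.073) = Φ(−1.19) = 12%.
- d = 1.0, TOST pass for a good site: Φ((0.180 − 0.333)/0.073) = Φ(−2.10) = 2%.
- d = 1.0, point-estimate flag for a good site: Φ((0.333 − 0.300)/0.073) = Φ(0.46) = 68%.

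**Joint results** (at least 200,000 simulated sets of four site means):

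| True pattern | Follow-up as TOST | Follow-up on point estimates |
|---|---|---|
| 2-2, D = 0.40 | all four pass 0.1%; all four fail 65% | no site flagged 28% |
| 2-2, D = 0.60 | all four fail 99.5% | all four flagged 73% |
| outlier, d = 0.4 | each good site passes 74% | only the outlier flagged 88% |
| outlier, d = 0.6 | each good site passes 39% | only the outlier flagged 75% |
| outlier, d = 1.0 | each good site passes 2%; all four fail 95% | each good site flagged 68% |

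Read as a two-sided difference test at 0.05, the follow-up flags each good site in 45% at d = 0.4 and 78% at d = 0.6.

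**Effect if four sites are pooled at D = 0.40.** Solve 0.5Φ(q + 0.2) + 0.5Φ(q − 0.2) = 0.05, which gives q = −1.677. Then Φ(−1.477) = 7.0% of women at the low sites and Φ(−1.877) = 3.0% at the high sites fall below the pooled 5th centile.

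**Grouping by the six pairwise TOSTs.** SE of a pair = √(2/250) = 0.089. A truly identical pair passes in 91.3%. Both identical pairs of a 2-2 split pass in 0.913² = 83%, and simulation gives 81 to 83% for the exact pattern at D from 0.35 to 1.0. The exact one-against-three pattern is found in about 80% for d from 0.4 to 1.5. With 200 per site these fall to about 67-68% and 63-64%.

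**The case against.** The strongest reply is that the article commits to less than this critique assumes. TOST is the only method it names. Under TOST a 2-2 split of 0.40 SD lets all four sites through in 0.1% of studies, so the plan almost never pools wrongly. Under-pooling is the safer error, and the Discussion says that each site is large enough for its own reference values (250 per site, against the 255 per time point that the centile calculation asks for). The pairwise results exist before the follow-up and would show either pattern. The clause on material change in centiles leaves room for judgement. The unseen analysis plan may add detail.

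Most of this stands, and it limits the harm. It does not rescue the contrast. The article assigns the choice of pooled sites to it, and the centile clause does not say which sites belong together. This is a stated rule that fails its purpose, not a missing detail.

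Two stronger readings are not supported. A reader might infer that the rule can never leave two pooled sites. It can: with means 0, 0.2, 0.4 and 0.6 SD, each extreme site is flagged in 91% and each middle site in 1% on point estimates, so the middle two remain. A reader might also infer that a 2-2 split is routinely pooled as one. The 28% at D = 0.40 belongs only to the point-estimate reading, and even there 72% of studies flag at least one site.

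**Conclusion.** The point holds, as something that should be fixed. The one-versus-rest contrast cannot identify the two pairs in a 2-2 split, and it rejects matching sites beside a distant one. The algebra holds for any sample size; the percentages assume 250 per site, equal SDs, a 0.3 SD margin and one-sided alpha 0.05. For one outlier of about 0.3 to 0.5 SD the step mostly works: on point estimates the outlier alone is flagged in 88% at 0.4 SD, and under TOST each good site passes in 74%, although all three pass together less often.

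Whether D or d reaches the damaging range is unknown, because the article gives no site differences in SD units. The document does not support the conclusion that the reference values would be wrong: the main consequence is avoidable under-pooling, softened by the centile clause and the site-specific fallback.

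**What to change.** Keep the trigger, stated explicitly as an estimated pairwise difference above 0.3 SD, and keep the centile clause. Replace the one-versus-rest follow-up with grouping by the six pairwise TOST results. Pool a set only if every pair within it is equivalent, take the largest such set, then check whether the remaining sites form a second set. Name a tie rule, for example the set with the smallest maximum pairwise difference.

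The change is to wording only and needs no new data or tests. The cost is that some nutrients will have more than one reference set. The trigger must stay: four truly identical sites pass all six TOSTs in only about 68%, so the all-pairs rule used alone would refuse full pooling in about 32% of such cases, whereas the trigger fires in about 0.4% of them.
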